### 2.5. Participants

We aim to enroll 144 children residing in the Maule region, Chile, who meet the following inclusion criteria: (i) enrolled in an educational center (school, college or kindergarten) that agrees to participate in the intervention; (ii) age range between 3 and 6 years old; (iii) attend ≥ 85% of the sessions scheduled for CMSI. Exclusion criteria will be the following: (i) children with musculoskeletal injuries or medical contraindications (i.e., congenital heart disease, fever, diarrhea or general malaise) that would prevent their normal performance in the assessments and intervention; and (ii) children with permanent educational needs mentioned in Decree No.83 of the Chilean Ministry of Education [20], such as visual, hearing, intellectual or multiple disabilities, dysphasia or autistic disorder. Figure 1 summarizes the selection process of the class groups and the number of children who will be included in the study.

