## Abstract

This study protocol aims to analyze and compare the effects of combined movement and storytelling intervention (CMSI) on fundamental motor skills (locomotor skills and object control), language development (language comprehension, language expression, vocabulary and language description), and physical activity levels (light intensity, moderate-to-vigorous intensity and sedentary time) in children aged 3 to 6 years. The sample will consist of 144 children from 12 class groups, randomly assigned to 3 experimental groups (*n* = 72 children) and 3 control groups (*n* = 72 children), belonging to 4 class groups of upper-middle-level classes (2 experimental and 2 control; 3 to 4 years), 4 transition level 1 classes (2 experimental and 2 control; 4 to 5 years) and 4 transition level 2 classes (2 experimental and 2 control; 5 to 6 years). The experimental groups will perform CMSI for 3 sessions per week (40 min per session) over 12 weeks (using one motor story per week), while the control groups will not receive any treatment. The main outcome will provide information about fundamental motor skills, language development, and physical activity levels. Our hypothesis indicates that CMSI has the potential to generate significant increases in selected assessments. If this intervention proves to be beneficial, it could contribute to preschool and school curricula.

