### 2.6. Intervention

The intervention will be implemented by early childhood educators, who will be trained about the objectives and contents of each session of CMSI that will be developed. Each session will take place in the classroom the preschoolers usually attend, which will depend on the admission policies of each educational community regarding the class levels (upper middle, transition level 1, and transition level 2). The intervention will last 12 weeks (36 sessions), distributed in 3 weekly sessions (Monday, Wednesday and Friday) of 40 min per session. CMSI is based on 2 previous studies [14,21], and a book related to CMSI [22]. Twelve unpublished motor stories will be distributed, one each week over 3 sessions, with the corresponding progressions for each session carried out. Thus, the children will be placed in a sequence of stories that begin with the presentation of a motivating character, who will accompany the children during the development of the whole story. The motor stories that will be developed each week are: (i) who I am; (ii) we go on an excursion; (iii) the school; (iv) the recess; (v) the weekend has arrived; (vi) visiting the park; (vii) my days in the field; (viii) my days at the beach; (ix) we go to the stadium; (x) we are going to know my environment; (xi) let’s go to the circus; (xii) tell me your adventures. The aim of the motor story translates into solving practical challenges while maintaining control, balance and coordination by combining various postures and movements such as throwing and receiving, moving on inclined planes and following rhythms, all in a variety of games and other activities [4,12,23].

The 40 min sessions will include three segments: (i) warm-up (5 min), which consists of joint mobility exercises and introduction to the motor story of the week; (ii) main part (25 min), which incorporates the narration of the motor story by the educator initially, as well as the participation of the children through their own corporeality with movements based mainly on FMSs (locomotion skills and object control), through two-way verbal interaction based on questions relating to the narration delivered by the educator or through direct verbal participation from each child; and (iii) cool down (10 min), where space is provided for the children to gradually return to calm, together with feedback on the content addressed during the session. Table 1 summarizes the materials and objectives of the weekly motor stories.

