### 2.7. Control Groups

The upper-middle-level control groups (n = 2 classes; n = 24 children), transition level 1 control groups (n = 2 classes; n = 24 children) and transition level 2 control groups (n = 2; n = 24 children) will participate in the assessments (initial and final) and will be asked to maintain their regular sessions at their educational establishments. At the end of the intervention period (according to the results obtained), the control group children, parents and/or legal guardians, managers and coordinators of each community will be contacted and provided with the material so that they can replicate the experience. In addition, the educators of these establishments (teachers and classroom assistants) will be trained in CMSI strategy.

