### 2.12. Intention-to-Treat Analysis

A two-factor repeated measures ANOVA will be used to determine the effects of the intervention on the outcomes (group × time). Post hoc tests will be performed with an alpha adjusted by Bonferroni to identify statistically significant differences. The effect sizes will be calculated utilizing Cohen’s d [36] within the group and between the groups, using the following equation: effect size = (post-mean − pre-mean)/standard deviation combined. The level of significance will be set at 5%. The intraclass correlation coefficient will be used to verify the measurement’s reliability, with a predetermined threshold of 0.80 being used to include the data in the analyses. Furthermore, logistic regression will be performed to identify the association of the physical activity level with FMSs, language development and morphological and sociodemographic variable factors. For all statistical analyses, the sociodemographic variables will be considered as moderators (covariates). 

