### 2.13. Analysis by Protocol

For this analysis, only children who have completed more than 85% of the sessions will be included. The same procedures will be performed as those indicated for the intention-to-treat analysis.

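### Attendance at 85% or more of CMSI sessions is listed as an inclusion criterion, so the analysis labelled intention-to-treat is open to post-randomisation selection in the experimental arm, and the per-protocol rule cannot be applied to controls

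*Protocol article*

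**What the plan says.** Section 2.5 opens its eligibility list with "We aim to enroll 144 children residing in the Maule region, Chile, who meet the following inclusion criteria". The third criterion in that list is attendance at no less than "85% of the sessions scheduled for CMSI". The list is not split by arm.

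Section 2.6 plans 36 CMSI sessions over 12 weeks. Section 2.8 places assignment at the first meeting, followed by two weeks of pre-tests and only then the programme. The Abstract describes the two arms with the words "while the control groups will not receive any treatment", and section 2.7 says that controls "will be asked to maintain their regular sessions at their educational establishments". It gives neither a number of such sessions nor an attendance threshold for them.

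Section 2.12 carries the intention-to-treat heading and specifies a group × time repeated measures ANOVA. It does not state which children enter. Section 2.13 says of the per-protocol analysis that "only children who have completed more than 85% of the sessions will be included", with the same procedures otherwise.

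Section 2.12 also introduces an intraclass correlation coefficient (ICC) for reliability, "with a predetermined threshold of 0.80 being used to include the data in the analyses".

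**The concern.** Eligibility should rest on what is known at enrolment. Attendance at CMSI sessions is an adherence measure that arises after allocation and exists in one arm only. Applied as eligibility, it takes children out of the experimental classes according to what happened during treatment, with no matching removal among controls.

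The Discussion names illness and injury as reasons why children may not complete the sessions, so those removed need not resemble those kept. If they would have progressed less, their removal favours CMSI. The protection given by randomising classes would then be lost in the very analysis meant to preserve it. The per-protocol analysis would offer no contrast either, because it would contain the same experimental children.

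**Working it through.** **Inputs from the protocol article.** 36 CMSI sessions (2.6); inclusion at 85% or more (2.5); per-protocol at more than 85% (2.13); about 72 children per arm (2.3); no CMSI sessions for controls (Abstract, 2.7).

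**Step 1: do the two attendance rules differ?** 0.85 × 36 = 30.6. A child with 30 sessions has 30/36 = 83.3% and fails both rules. A child with 31 has 31/36 = 86.1% and passes both. The difference between at least and more than has no effect, and the cut is 31 sessions under either wording. With the inclusion criterion in force, the intention-to-treat and per-protocol sets hold the same experimental children.

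**Step 2: what do the rules do to controls?** The same reading has to be used for both sections.

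| Reading | Criterion (iii), 2.5 | Per-protocol rule, 2.13 |
|---|---|---|
| Literal (CMSI sessions, all children) | A control attends 0 of 36, so none of the 72 is eligible | No control qualifies |
| Workable (experimental arm only) | Poor attenders leave one arm only | No rule for controls |
| Charitable (controls' regular sessions count) | Not open: the text names CMSI | Cannot be applied: no number or threshold given |

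Since 72 controls are planned, the workable reading is the one to carry forward.

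**Step 3: how many children could be removed?** The document gives no attendance rate. As an illustration, assume independent attendance at each session with probability p. The expected number kept is 72 × P(X ≥ 31), with X binomial (36, p).

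| p (assumed) | Kept of 72 | Removed |
|---|---|---|
| 0.95 | 71.4 | 0.6 |
| 0.90 | 61.5 | 10.5 |
| 0.85 | 38.9 | 33.1 |
| 0.80 | 17.7 | 54.3 |

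**Step 4: how far could the contrast move with no true effect?** Each child has a pre-test, so the relevant correlation r is between attendance and change. Assume that the two are jointly normal and that the share k with the highest attendance is kept. Then shift = r × φ(z)/k in SDs of change, where z = Φ⁻¹(1 − k). For example, k = 0.85 and r = 0.2 give 0.2 × 0.2332/0.85 = 0.055.

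| Share removed (assumed) | r = 0 | r = 0.1 | r = 0.2 | r = 0.3 |
|---|---|---|---|---|
| 5% (3.6 of 72) | 0 | 0.011 | 0.022 | 0.033 |
| 15% (10.8 of 72) | 0 | 0.027 | 0.055 | 0.082 |
| 30% (21.6 of 72) | 0 | 0.050 | 0.099 | 0.149 |

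None of these shares or correlations comes from the document. The 15% expected loss in section 2.3 is not defined as missed sessions, so it does not fix a row.

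**The case against.** The strongest reply is that criterion (iii) is a misplaced adherence rule. The article has separate intention-to-treat and per-protocol sections, and section 2.13 presents the attendance restriction as belonging to that analysis, which suggests that the other has none. An article also condenses, and a full definition of the intention-to-treat set may stand elsewhere. This much holds: the document does not establish which children will finally be analysed, and the missing definition is not itself the fault. What remains is that section 2.5 states the criterion outright, and nothing shown reconciles it with an intention-to-treat analysis.

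Three stronger readings are tempting, and the text does not support them.

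- A reader might infer that the per-protocol rule excludes every control. Section 2.13 speaks of sessions without naming CMSI, section 2.7 uses the same word for the controls' usual activities, and the planned group × time ANOVA needs controls. It would also be inconsistent to take 2.13 literally while reading 2.5 as confined to the experimental arm. The supportable statement is that no usable rule for controls is given.
- A reader might infer a material bias because healthier or more engaged children are kept. A stable trait that affects pre-test and post-test equally cancels in a group × time contrast. Only correlation with change matters, and near-full attendance would leave almost nobody to remove.
- A reader might infer that the ICC threshold lets a primary outcome be dropped after its data have been seen. Section 2.12 does not say that the ICC is computed on trial data or when. Certifying assessors beforehand would fit the words. The threshold is also not specific to one arm, so it is a separate and lesser matter of wording.

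**Conclusion.** The point holds as a fault in the text. Section 2.5 uses a post-randomisation adherence measure as eligibility. This cannot be met by controls if read literally, and acts on one arm only if read workably. It makes the intention-to-treat and per-protocol sets coincide in the experimental arm at 31 or more of 36 sessions. That conclusion rests only on the document's own figures.

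The size of any resulting bias cannot be computed from the document. Under the assumptions shown it ranges from near zero to about 0.15 SD of change, the upper end needing 30% removed and a correlation of 0.3 between attendance and change. The direction is likewise not fixed by the text; it favours CMSI if poor attenders would have improved less.

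Sections 2.5, 2.12 and 2.13 need to be reconciled before any child is excluded for attendance, since outcome data not collected on excluded children may be impossible to recover. The ICC wording is secondary.

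**What to change.** 1. Delete inclusion criterion (iii) from section 2.5 and record attendance as an adherence measure.
2. State in section 2.12 that the intention-to-treat set is every enrolled child in a randomised class, analysed as allocated whatever the attendance, and seek post-tests from all of them.
3. Keep the 85% rule only in section 2.13, for a supportive per-protocol set. Write it as at least 31 of the 36 sessions, and add an equivalent rule for controls. One option is attendance on the same scheduled school days, if attendance is recorded in both arms. School-day attendance is only a proxy for attending a 40-minute session, which should be acknowledged.
4. Secondary: reword the ICC sentence in section 2.12 so that reliability is established against 0.80 before the pre-test and reported, and is not used to drop collected outcome data.

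The cost is mainly wording. Control attendance must be recorded, which the document does not now provide for, and the intention-to-treat effect may come out slightly smaller.

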### 2.6. Intervention

The intervention will be implemented by early childhood educators, who will be trained about the objectives and contents of each session of CMSI that will be developed. Each session will take place in the classroom the preschoolers usually attend, which will depend on the admission policies of each educational community regarding the class levels (upper middle, transition level 1, and transition level 2). The intervention will last 12 weeks (36 sessions), distributed in 3 weekly sessions (Monday, Wednesday and Friday) of 40 min per session. CMSI is based on 2 previous studies [14,21], and a book related to CMSI [22]. Twelve unpublished motor stories will be distributed, one each week over 3 sessions, with the corresponding progressions for each session carried out. Thus, the children will be placed in a sequence of stories that begin with the presentation of a motivating character, who will accompany the children during the development of the whole story. The motor stories that will be developed each week are: (i) who I am; (ii) we go on an excursion; (iii) the school; (iv) the recess; (v) the weekend has arrived; (vi) visiting the park; (vii) my days in the field; (viii) my days at the beach; (ix) we go to the stadium; (x) we are going to know my environment; (xi) let’s go to the circus; (xii) tell me your adventures. The aim of the motor story translates into solving practical challenges while maintaining control, balance and coordination by combining various postures and movements such as throwing and receiving, moving on inclined planes and following rhythms, all in a variety of games and other activities [4,12,23].

The 40 min sessions will include three segments: (i) warm-up (5 min), which consists of joint mobility exercises and introduction to the motor story of the week; (ii) main part (25 min), which incorporates the narration of the motor story by the educator initially, as well as the participation of the children through their own corporeality with movements based mainly on FMSs (locomotion skills and object control), through two-way verbal interaction based on questions relating to the narration delivered by the educator or through direct verbal participation from each child; and (iii) cool down (10 min), where space is provided for the children to gradually return to calm, together with feedback on the content addressed during the session. Table 1 summarizes the materials and objectives of the weekly motor stories.

### 2.7. Control Groups

The upper-middle-level control groups (n = 2 classes; n = 24 children), transition level 1 control groups (n = 2 classes; n = 24 children) and transition level 2 control groups (n = 2; n = 24 children) will participate in the assessments (initial and final) and will be asked to maintain their regular sessions at their educational establishments. At the end of the intervention period (according to the results obtained), the control group children, parents and/or legal guardians, managers and coordinators of each community will be contacted and provided with the material so that they can replicate the experience. In addition, the educators of these establishments (teachers and classroom assistants) will be trained in CMSI strategy.

### 2.8. Outcomes and Procedures

The first meeting will be to obtain the agreement of the educational establishments and educators, to obtain the necessary signatures of informed consent and to explain the scope and aim of the study; also, the children will be randomly assigned to the intervention groups. During the following 2 weeks, the first assessments (pre-tests) will be carried out, before the 12-week CMSI is implemented; finally, the second assessments (post-tests) will be administered. One of the researchers will supervise all of the assessments and CMSI, and there will be a predefined order that will be followed by expert personnel in the assessments: (i) FMSs (physical education teacher specializing in early childhood care); (ii) language development (kindergarten teacher); (iii) physical activity level (physical education teacher); (iv) morphological variables (anthropometrist); and (v) sociodemographic variables (kindergarten teacher and physical education teacher). Figure 2 shows a summary of the assessments and sessions that are usually part of CMSI.

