### 2.3. Sample Size Calculation

Twelve children will be recruited from each class group (without gender distinction). The distribution of the class groups (12 class groups) will be in 3 experimental groups (6 class groups, n ± 72 children) and 3 control groups (6 class groups, n ± 72 children). The distribution by clusters or strata is justified by the fact that the use of individual randomization would imply a high probability of contaminating the control groups since it is unfeasible to prohibit children from interacting in school classrooms or recreational spaces (i.e., playgrounds, hallways, laboratories), which is where the study intervention will be carried out [18,19]. In addition, in the Maule region (one of the sixteen regions into which to Chile is divided; located in the center of the country and bordered to the north by the O’Higgins region, to the east by the provinces of Mendoza and Neuquén belonging to Argentina, to the south by the Ñuble region and to the west by the Pacific Ocean), there are 54 educational establishments that provide preschool education with an enrollment of approximately 1080 children. 

The sample size calculation indicates that the ideal number of participants per group is 10. As agreed in a previous study by Eyre et al. [15], we will use a mean difference of 3.22 total score of locomotor skill domains for this calculation as the minimum difference necessary for substantial clinical relevance, with a standard deviation of 0.70 points, considering an alpha level of 0.05 with a power of 80% and an expected loss of 15%. The GPower program (version 3.1.9.6, Franz Faul, Universiät Kiel, Kiel, Germany) will be used to calculate the statistical power. 

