### 2.4. Randomization and Blinding

The 12 class groups will be selected from 4 upper-middle-level classes (2 experimental and 2 control; age range between 3 and 4 years), 4 transition level 1 classes (2 experimental and 2 control; age range between 4 and 5 years) and 4 transition level 2 classes (2 experimental and 2 control; age range between 5 and 6 years), which will be randomized with stratified sampling [16]. This consists of segmenting the classes that agree to participate in the study according to educational levels (strata) and then performing a random sampling on each of them, using R statistical software, version 4.1.2. This study is considered double-blind because the measurements will be performed by professionals who are external to the research. 

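### Section 2.8 puts random assignment before the pre-tests and names children as the unit, against the class randomisation in 2.3 and 2.4; baseline scores are open to bias that would enter the group × time effect

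*Protocol article*

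**What the plan says.** Section 2.8 is the only place in the protocol article that sets out the order of procedures. The first meeting is to secure the agreement of establishments and educators, and "to obtain the necessary signatures of informed consent and to explain the scope and aim of the study". The same sentence then turns to allocation, and the next to baseline: "also, the children will be randomly assigned to the intervention groups. During the following 2 weeks, the first assessments (pre-tests) will be carried out", ahead of the 12-week intervention.

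On the unit of allocation, section 2.3 explains the cluster design by saying that "the use of individual randomization would imply a high probability of contaminating the control groups". Section 2.4 describes "segmenting the classes that agree to participate in the study according to educational levels (strata"), followed by random sampling within each level, with two experimental and two control classes per level. Section 2.3 adds: "Twelve children will be recruited from each class group".

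On who is present and who scores:
- Section 2.4 calls the study double-blind because the measurements are made by professionals from outside the research.
- Section 2.8 has one researcher supervise both the assessments and the intervention.
- Section 2.9.2 has a classroom assistant in the room during the language test.
- Section 2.6 has early childhood educators deliver the intervention.

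Section 2.12 tests the intervention effect as group × time in a two-factor repeated measures ANOVA.

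**The concern.** Two things are wrong on the face of the text. First, 2.8 assigns children, while 2.3 and 2.4 assign classes and give a reason why individual assignment would not work here. Second, 2.8 places assignment before baseline.

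The order matters because the pre-test is half of the effect estimate. Motor skills are scored by an observer against performance criteria and language is tested face to face, so both can be affected by what the people in the room expect. If they know a class's arm when the pre-test is taken, the baseline no longer has the protection that randomisation should give it. A baseline already collected under known allocation cannot be repaired by analysis.

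**Working it through.** The article gives no figure on this point, so the check compares the sections and then asks what a baseline error does to the planned contrast.

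1. **Order.** Section 2.8 gives: agreement, consent and assignment at the first meeting; pre-tests over the following 2 weeks; 12 weeks of intervention; post-tests. No other section gives a different order. As written, every pre-test follows allocation.

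2. **Unit.** Section 2.4 has 3 levels × 4 classes = 12 classes, two per arm in each level. With 12 children per class this is 12 × 12 = 144 children, which matches the planned total. Section 2.7 counts controls in the same way: 2 classes × 12 = 24 children per level. All of these fit class allocation. Only the phrase in 2.8 names children.

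3. **Who could know the arm at pre-test.** Educators of experimental classes must learn their arm in order to deliver the intervention. The supervising researcher oversees both the assessments and the intervention. The classroom assistant at the language test is, by role, school staff. The assessors are said to be external, which describes where they come from, not what they know. The text states neither that they know the allocation nor that they do not.

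4. **Effect on the contrast.** Write E and C for the arms. The group × time term is the difference in change:

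   Δ = (post_E − pre_E) − (post_C − pre_C).

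   - *Scoring error e at pre-test only, in arm E.* pre_E becomes pre_E + e, so Δ becomes Δ − e. The whole error enters. Under-scoring the experimental arm at baseline inflates the effect; over-scoring shrinks it.
   - *Stable difference r from recruitment, in arm E.* Both post_E and pre_E rise by r, so (post_E + r) − (pre_E + r) = post_E − pre_E and Δ is unchanged. Recruitment would bias Δ only through different growth or regression to the mean.

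5. **Which outcomes.** Step 4 applies to the motor and language scores. Physical activity is recorded by accelerometer (2.9.3), so scorer error does not arise there.

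6. **Size.** The article gives nothing from which e could be estimated. If e were assumed to be 0.1 to 0.2 SD, Δ would move by the same 0.1 to 0.2 SD. That range is purely an assumption and has no source in the document.

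**The case against.** The strongest reply is that this is loose wording in a condensed article. Consent is listed before assignment within the meeting, and 2.4 has classes agree first and then be sampled. The natural reading is therefore that agreement and consent precede the draw. Sections 2.3, 2.4 and 2.7 consistently treat the class as the unit, and nobody is likely to randomise individual children because of one phrase. The study is described as double-blind with outside assessors, and allocation after consent but before baseline can be acceptable when participants are already fixed and assessors are blind. Details of concealment may sit in the full protocol.

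Much of this stands, and it limits the point in three ways:

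- A reader might infer that parents and educators choose the 12 children per class knowing the arm. The text does not say so. It does not say that allocation is disclosed at the meeting or that the children are selected afterwards. It also does not fix that the list is closed first, so this remains a possible risk only.
- A reader might infer that the assessors know the allocation. The text does not say that either.
- A reader might scale the bias against the locomotor SMD of 0.44 cited in the Introduction. That figure comes from other programmes lasting 17 to 21 weeks and is not this trial's planning effect. The size of the error would itself be a guess.

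What the reply does not remove is the stated sequence. Pre-tests after assignment is what 2.8 says, not a missing detail, and the contradiction over the unit is also in the text. Describing assessors as external does not protect a pre-test taken after allocation unless they are also unaware of it.

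**Conclusion.** The point holds in a limited form. Section 2.8 contradicts 2.3 and 2.4 on the unit of allocation, and it places the motor and language pre-tests after allocation without stating that those who score or supervise them are unaware of it. A pre-test scoring error that differs by arm would enter the group × time effect in full.

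This is a risk created by the stated order, not a demonstrated bias. It depends on the allocation being known to someone able to influence the pre-test, which the staffing in 2.8 and 2.9.2 makes plausible but does not prove. Its size cannot be estimated from the document. Biased recruitment is not shown, and a stable difference in who is recruited would largely cancel in the change contrast. Scorer bias does not apply to the accelerometer outcomes.

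**What to change.** In 2.8, replace the statement that children are assigned with: *the classes will be randomly assigned within educational level*. Then fix the order of steps:

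1. establishment agreement and parental consent;
2. list of 12 children per class closed;
3. pre-tests completed;
4. class allocation drawn and disclosed;
5. educator training and week 1.

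If that order is not feasible, state that allocation is concealed from the pre-test assessors and from the supervising researcher until the pre-tests are complete.

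The cost is a rewording and a reordering of steps. Educators of experimental classes would be trained after the pre-tests, which may add some days before week 1. No change to sample size, outcomes or analysis is needed.
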